**Figure 2 Fig2:**
[figure not shown]
Application of Rogers’ (1962) product adoption process to the study interventions.

Participants in both the intervention 1 and intervention 2 groups will receive an information pack describing PARC and the various physical activity facilities available at the centre. This information is designed to target the ‘awareness’, ‘interest’, and ‘evaluation’ phases of Rogers’ [12] product adoption process outlined in Figure 2. Intervention 1 and intervention 2 group participants will also receive a free pass to PARC, allowing them to try out the facility as per the ‘trial’ phase of Rogers’ [12] product adoption process.

Participants in the intervention 2 group will receive additional content designed to target the ‘adoption’ and ‘maintenance’ phases of Rogers’ [12] product adoption process. This content will be delivered over a 24 month period as part of a customer relationship management (CRM) system, a commercial marketing technique designed to manage a firm’s interactions with current and future customers [14] and which has been found to maximise customer loyalty and retention [15]. An overview of the key CRM contact points with intervention 2 participants is presented in Figure 3. Specifically, upon redeeming the free PARC pass, intervention 2 participants will receive a message congratulating them for redeeming their pass and encouraging them to return to the centre soon. Two months before the pass expires, those who are yet to redeem the free pass will receive a telephone call reminding them that the pass will be expiring soon. Finally, those who have attended PARC at least once but who have not returned to the facility in the last two months will receive a follow-up telephone call to encourage their continued use of the facility.

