**Figure 3 Fig3:**
[figure not shown]
Overview of the customer relationship management (CRM) process for intervention 2 participants. Legend: Grey-coloured boxes denote participant contact points.

Several other contact points will be integrated into the CRM system. For example, intervention 2 participants will receive follow-up phone calls every 6 months to discuss their physical activity goals, identify strategies for overcoming barriers to physical activity, and encourage their usage of PARC. Intervention 2 participants will also receive a quarterly newsletter aimed at motivating regular physical activity and identifying strategies to overcome common barriers to engaging in regular physical activity. Embedded within the newsletter will be content espousing the benefits of conducting regular physical activity at PARC. Finally, participants will receive personalised, hand-written cards for their birthday and in the lead-up to the end of year festive season. Each card will encourage recipients to achieve their physical activity goals.

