#### Data analysis

Process data about intervention dose delivered, reach, and dose received will be summarised using descriptive statistics. Transcripts from semi-structured interviews about the contextual factors affecting use of PARC and satisfaction with the CRM activities will be analysed using thematic analysis [35]. Bivariate and multivariate statistical tests will be used to analyse differences between the control, intervention 1, and intervention 2 groups on the primary outcome measures across the three data collection points. In the multivariate analyses, group status (i.e., control, intervention 1, intervention 2) will be entered as a covariate to calculate intervention effect sizes. Mediation and moderation analyses [36] will also be used to examine whether the secondary outcome variables influence the intervention effect sizes. Analysis will be undertaken by intention to treat and by treatment received according to the dose received of marketing components.

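### The treatment-received analysis is confounded by attendance for PARC usage, because part of the marketing dose follows from attending or not attending; it is not ranked below intention to treat

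*Protocol article*

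**What the plan says.** The protocol article's Data analysis section commits to two analyses in one sentence: "Analysis will be undertaken by intention to treat and by treatment received according to the dose received of marketing components". Neither is named as the basis for conclusions.

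The Intervention procedure section makes three intervention 2 contacts depend on attendance:
- Redemption message: "upon redeeming the free PARC pass, intervention 2 participants will receive a message congratulating them for redeeming their pass".
- Expiry call, two months before the pass lapses: "those who are yet to redeem the free pass will receive a telephone call reminding them that the pass will be expiring soon".
- Lapse call, made to "those who have attended PARC at least once but who have not returned to the facility in the last two months".

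The same section schedules other contacts whatever the attendance: "intervention 2 participants will receive follow-up phone calls every 6 months"; "Intervention 2 participants will also receive a quarterly newsletter"; and "participants will receive personalised, hand-written cards for their birthday", with a further card before the festive season.

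The Process evaluation measures section says that the CRM database logs delivery of each component. It then says that use of the free pass is recorded in both intervention groups, and that dose received is also measured by asking intervention 2 participants about their use and recall of the materials. The natural reading of that sequence is that pass use counts as a dose-received measure. The Primary outcome measures section lists PARC usage first, and the Sample size section is built on regular use of PARC.

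**The concern.** A comparison by dose received describes a treatment effect only if dose is not itself driven by the outcome. Here part of it is. Redeeming the pass is a PARC visit, so on that component dose and outcome overlap by definition, in intervention 1 as well as intervention 2. The three triggered contacts are sent because the participant has attended, has not attended, or has attended and then stayed away. Recall is asked at follow-up, when users of the facility may remember more than non-users.

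At stake is whether the CRM adds anything to the information pack and free pass, which is one of the two contrasts on which the trial is sized and which the Discussion calls a key innovation. A null randomised result could be reported beside an apparent dose effect produced only by who attended, and the plan does not say how a reader should weigh the two.

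**Working it through.** **The plan's own figure.** The Sample size section gives 300 per arm for 20% vs 10% and for 30% vs 20%, at 80% power. With two-sided 5% (inferred from the 95% confidence stated), pooled variance and no continuity correction:

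n = [1.96·√(2·p̄(1−p̄)) + 0.842·√(p1(1−p1) + p2(1−p2))]² / (p1−p2)²

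This gives 294 per arm for 30% vs 20% and 199 for 20% vs 10%. The 300 is reproduced, so the planned effect to compare against is 10 points.

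**Set-up under no CRM effect.** Regular use is p = 20% in both intervention arms (the plan's intervention 1 rate). The randomised contrast is then 20% vs 20%, a difference of 0. The documents give no redemption or lapse rates, so these are assumptions:
- r, the share redeeming the pass: 30% to 80%.
- s, the share of regular users who redeem: 100% or 80%.
- a, the share of regular users who ever get a lapse call: 10% to 60%. Among other attenders: 90%.

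**Redemption message.** Regular use is p·s/r in recipients and p(1−s)/(1−r) in non-recipients.

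| r | s = 100% | s = 80% |
|---|---|---|
| 30% | 0.20/0.30 = 67% vs 0% | 0.16/0.30 = 53% vs 0.04/0.70 = 6% |
| 50% | 0.20/0.50 = 40% vs 0% | 0.16/0.50 = 32% vs 0.04/0.50 = 8% |
| 80% | 0.20/0.80 = 25% vs 0% | 0.16/0.80 = 20% vs 0.04/0.20 = 20% |

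Grouping by pass redemption gives the same table, because the message follows redemption. The expiry call gives the mirror image if nobody redeems after the call.

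**Could chance hide it?** Take r = 50%, s = 100% and 300 per arm. Message recipients (60/150) against all of intervention 1 (60/300) differ by 20 points. The pooled rate is 120/450 = 0.267, the standard error is √(0.267·0.733·(1/150 + 1/300)) = 0.044, and z is about 4.5.

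**Lapse call.** Regular use in recipients is p·a / [p·a + 0.9(r − p·s)]. In non-recipients it is p(1−a) divided by the remaining proportion of the arm.
- r = 30%, s = 100%, a = 60%: 0.12/0.21 = 57% vs 0.08/0.79 = 10%.
- r = 30%, s = 100%, a = 10%: 0.02/0.11 = 18% vs 0.18/0.89 = 20%.
- r = 80%, s = 80%, a = 10%: 0.02/0.596 = 3% vs 0.18/0.404 = 45%.

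The sign is undetermined. In this set-up everyone gets either the message or the expiry call, so having two or more types of triggered contact is the same as having had a lapse call, with the same results.

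**Recall.** If 70% of regular users and 40% of others recall the materials (assumed), regular use is 0.14/(0.14 + 0.32) = 30% in those who recall and 0.06/(0.06 + 0.48) = 11% in those who do not. If recall is unrelated to use, it is 20% vs 20%.

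**Scheduled contacts.** Over 24 months the stated frequencies give 24/6 = 4 calls, 24/3 = 8 newsletters and about 2 cards × 2 years = 4, or 16 in all. Sending them does not depend on attendance, so the trigger rule induces no difference through them.

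**The case against.** The strongest reply is that the analysis uses dose received, which the Process evaluation measures section separates from dose delivered. Being sent a triggered contact is delivery, and nothing says that it defines an analysis group. How dose is scored may properly sit in a statistical analysis plan. This stands in part: the document does not fix the dose variable, so no single figure above is the bias of the planned analysis. It does not remove the problem, because pass use and recall, the dose-received measures the article describes, are also tied to attendance.

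Four stronger readings are tempting, and the documents do not support them.
- A reader might infer that the analysis is bound to show a large effect. About 16 contacts are scheduled regardless of attendance against three triggered types, the message and expiry call pull in opposite directions, and some scenarios give almost no difference.
- A reader might infer that the lapse call must look harmful, since its recipients stopped coming. They are also people who came at least once, while the comparison group includes everyone who never came. A two-month gap within 24 months does not rule out regular use.
- A reader might infer that the dose analysis could displace the randomised result. Intention to treat is named first, group status is entered to calculate the effect sizes, and the sample size concerns randomised arms. Nothing gives the dose analysis authority over these; the text only leaves the two unranked.
- A reader might extend the circularity to every primary outcome. It is direct only for PARC usage. For the others, any confounding runs indirectly through attendance and engagement.

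**Conclusion.** The point holds as a flaw in a stated analysis. For PARC usage, the treatment-received comparison is confounded by attendance and can show a sizeable difference in either direction with no CRM effect. In the scenarios worked, the spurious difference for the redemption message runs from 67 points to none, and for the lapse call from about +47 to about −41 points, against a planned effect of 10. These sizes rest on assumed redemption, lapse and recall rates and on a dose definition that the article does not give. That pass use counts as dose received is a reading of the Process evaluation measures section, though the natural one. Intention to treat is unaffected, and the sample size needs no change.

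**What to change.** 1. State that conclusions about intervention effects rest on intention to treat alone.
2. Label the treatment-received analysis exploratory and non-causal.
3. Exclude pass redemption and the three attendance-triggered contacts from any dose variable set against PARC usage. Build that variable only from delivered scheduled calls, newsletters and cards, as logged in the CRM database. Even then, who can be reached by telephone may reflect engagement, so the label in step 2 stays.
4. Report pass use and the triggered contacts descriptively in the process evaluation.
5. If a randomisation-based supportive estimate is wanted, use a complier-average effect of intervention 2 vs intervention 1, with receipt defined as being reached by the CRM programme as a whole. Receipt defined by scheduled contacts only would not do: assignment to intervention 2 also delivers the triggered contacts, which may act on attendance themselves, so the exclusion restriction would fail. If nearly everyone is reached, this estimate will be close to intention to treat.

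The cost is wording and a little analysis. The downside is a less informative supportive analysis with wider intervals. Recruitment, data collection and delivery do not change.

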#### Economic evaluation

Cost-effectiveness analyses for interventions 1 and 2 will compare gains in the primary outcome variables relative to controls, taking into account the additional costs associated with implementing these interventions. In addition, the impact of interventions 1 and 2 on PARC membership and membership renewal, once participation incentives end, will be used to explore the potential implications of marketing interventions for promoting and maintaining memberships and revenues.

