### Statistical considerations

#### Sample size

Sample size calculations have been undertaken to determine the number of participants needed to show a significant difference in attendance rates at PARC. To be conservative in sample size calculations (i.e., avoid lack of power), it is assumed that 10% of control group participants will become regular users of PARC. Thus, a sample size of 300 in each arm of the study will be required to show with 95% confidence limits and 80% power: (i) a 10% difference in outcome between participants in intervention 1 and the control group (i.e., 20% vs. 10%); and (ii) a 10% difference between those in intervention 1 and intervention 2 (i.e., 30% vs. 20%). If fewer than 10% of control group participants attend PARC regularly, this sample size will enable detection of smaller differences between participants in the control and intervention groups. To accommodate attrition over the course of the two year study, the target sample size will be inflated to 400 per group for the two intervention groups and 500 for the control group because of the potential reduced engagement that control group participants may have with the study.

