## Discussion

A large proportion of the Australian population do not meet the recommended levels of physical activity, thereby forgoing the protective health benefits that physical activity confers. Strategies aimed at increasing physical activity levels, such as encouraging surrounding populations to make use of new physical activity facilities or other changes to the built environment, are therefore of particular importance. The MOVE study will consequently assess whether two commercial marketing approaches are equally effective in motivating communities to engage with and utilise a new pool and gym facility. This is to our knowledge the first such evaluation to be undertaken and represents a central contribution of the MOVE study.

Leveraging commercial marketing techniques to improve the wellbeing of individuals or communities (i.e., ‘social marketing’ [37]) is not unprecedented, with such techniques playing an important role in addressing a range of public health challenges [38]. What has yet to be examined is whether these techniques can be effectively utilised to encourage inactive populations to make use of new physical activity facilities. This is particularly true for CRM, a commercial marketing technique that has been recognised as having potential efficacy in social marketing contexts [39], but which has yet to have these novel applications empirically tested. Comparing the efficacy of CRM and non-CRM social marketing interventions within the context of encouraging ongoing attendance at physical activity facilities therefore represents a key innovation of the MOVE study.

A second innovative feature of the MOVE study relates to segmentation, another principle widely employed in social marketing settings [11]. Segmentation represents an acknowledgement that certain groups within a population may share similarities on various social, psychological, or demographic dimensions, and that developing interventions that target one or more of these groups may increase the efficacy of those interventions [11,40]. The MOVE study will utilise a post-intervention segmentation approach in that it will test for potential moderators of intervention effectiveness to determine whether some population groups may be particularly responsive to the interventions being tested. This, in turn, could guide future decisions about which population groups to preferentially target in interventions.

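### The cost-effectiveness plan compares both interventions with control but does not plan the comparison of intervention 2 with intervention 1, which is the one that values CRM

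*Protocol article*

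**What the plan says.** The Economic evaluation section of the protocol article names one comparator for both interventions: "Cost-effectiveness analyses for interventions 1 and 2 will compare gains in the primary outcome variables relative to controls". On the cost side, the same sentence describes the analysis as "taking into account the additional costs associated with implementing these interventions". Its second sentence, on memberships and revenue, names no comparator and is not a cost-per-gain analysis.

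The Intervention procedure section makes the arms nested. Both active arms get the information pack, and "Intervention 1 and intervention 2 group participants will also receive a free pass to PARC". Then "Participants in the intervention 2 group will receive additional content designed to target the ‘adoption’ and ‘maintenance’ phases", and "This content will be delivered over a 24 month period as part of a customer relationship management (CRM) system".

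Other parts of the article treat the step from intervention 1 to intervention 2 as central:
- The Sample size section sets as its second target "a 10% difference between those in intervention 1 and intervention 2 (i.e., 30% vs. 20"%).
- The Discussion presents "Comparing the efficacy of CRM and non-CRM social marketing interventions" as a main novelty of the study.
- The abstract's Discussion paragraph says the findings may show whether CRM systems are cost-effective.
- The end of the Discussion stresses financial sustainability and adoption by facility operators.

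**The concern.** The three arms are mutually exclusive options, each built on the one before: nothing, pack and pass, pack and pass with CRM. An operator who can already offer the pack and pass needs to know what CRM adds for its additional cost. The planned ratio for intervention 2 answers a different question, namely the value of the whole bundle against doing nothing. The effectiveness part of the plan covers the CRM step; the economic part, as written, does not. The abstract's statement about the cost-effectiveness of CRM would then rest on a figure that does not isolate CRM. This is a comparator that the article states, not a detail it has left to a fuller plan.

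**Working it through.** **Inputs.** From the Sample size section: "it is assumed that 10% of control group participants will become regular users of PARC"; 20% in intervention 1; 30% in intervention 2; 80% power; 95% confidence, read as two-sided 5%. The article gives no costs. Let c1 and c2 be the extra cost per person of interventions 1 and 2 over control, and e1 and e2 their gains over control. At the planning rates e1 = 0.20 − 0.10 = 0.10 and e2 = 0.30 − 0.10 = 0.20. Regular use of the facility (PARC) serves as the effect measure here because it is the only outcome with stated rates.

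**Step 1. Reproduce the 300 per arm.** Pooled-variance formula for two proportions: n = [1.96·√(2p̄(1−p̄)) + 0.842·√(p₁(1−p₁) + p₂(1−p₂))]² / (p₂−p₁)².
- 30% vs 20%: [1.96·√0.375 + 0.842·√0.37]² / 0.01 gives 294.
- 20% vs 10%: [1.96·√0.255 + 0.842·√0.25]² / 0.01 gives 199.

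The stated 300 therefore reproduces for intervention 2 against intervention 1. With 300 per arm, power is 0.81 for that contrast and 0.93 for intervention 1 against control. The contrast that drives the sample size is the one missing from the cost-effectiveness plan.

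**Step 2. What the planned ratio measures.**
- Planned, intervention 2 vs control: c2/e2.
- Value of CRM, intervention 2 vs intervention 1: (c2 − c1)/(e2 − e1).

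The first is a weighted average of the pack-and-pass ratio and the CRM ratio: c2/e2 = (e1/e2)·(c1/e1) + ((e2−e1)/e2)·((c2−c1)/(e2−e1)). At the planning rates each weight is 0.10/0.20 = 1/2. The planned ratio is lower than the CRM ratio, and so flatters CRM, exactly when c2/c1 > e2/e1. Here e2/e1 = 0.20/0.10 = 2.

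**Step 3. Size across assumed cost ratios.** Cost per extra regular user in units of c1. Intervention 1 vs control is 1/0.10 = 10 throughout.

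| c2/c1 (assumed) | Int. 2 vs control = (c2/c1)/0.20 | Int. 2 vs int. 1 = (c2/c1 − 1)/0.10 | CRM ratio ÷ planned ratio |
|---|---|---|---|
| 1.5 | 7.5 | 5 | 0.67 |
| 2 | 10 | 10 | 1.00 |
| 3 | 15 | 20 | 1.33 |
| 5 | 25 | 40 | 1.60 |
| 10 | 50 | 90 | 1.80 |

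**Step 4. Sensitivity to the effects (assumed values).** If CRM added 5 points instead of 10, the break-even would be 0.15/0.10 = 1.5. If intervention 1 gained 5 points and intervention 2 gained 20, it would be 0.20/0.05 = 4. The break-even moves with the effects, so the direction of the error cannot be fixed in advance.

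**Step 5. Limiting case.** Suppose CRM adds nothing and both active arms reach 20%. Intervention 2 is then dominated for any c2 > c1: it costs more for the same gain. The comparison with control still yields a finite c2/0.10. This case needs no assumed cost ratio, only that CRM costs something.

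**The case against.** A reader might infer that intervention 2 will look better value than it is. The documents do not support that. They price neither the pass nor CRM, and the Background calls both interventions low intensity. At the planning rates the ratio against control flatters CRM only if c2 exceeds twice c1; below that, it makes CRM look dearer than it is. Two years of calls, newsletters and cards against one pack and one pass make c2 > 2·c1 plausible, but not established.

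A reader might also infer that nearly all of intervention 2's gain comes from the free pass. At the planning rates CRM supplies 10 of the 20 points, that is half. If it supplied very little, the three-group comparison in the Data analysis section would show it.

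Nor is it right that the cost of CRM can never be set against its gain. Both arms share one control group, so the point estimate follows by subtraction if costs and gains are reported separately for each arm. This objection stands. But the two ratios alone do not give the incremental ratio, the shared control arm means that they do not give its interval, and the section does not commit to reporting either.

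Finally, a short article may leave the methods for intervals and dominance checks to a fuller plan, and their absence is no fault. The point here is the comparator, which the article does state.

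**Conclusion.** The point holds in a limited form. The economic section plans comparisons with control and does not plan intervention 2 against intervention 1, although the arms are nested, the sample size is set by that step and the abstract anticipates evidence on the cost-effectiveness of CRM. The planned ratio for intervention 2 can misstate the value of CRM in either direction. Over assumed c2/c1 from 1.5 to 10, the true CRM ratio runs from 0.67 to 1.8 times the planned one, equal at 2. These figures rest on the planning rates, on regular PARC use as the effect measure and on cost ratios that the documents do not give. That the ratio against control stays finite when CRM adds nothing does not depend on the cost ratio. The effectiveness analysis and the sample size are unaffected.

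**What to change.** Amend the Economic evaluation section to:
- order the three arms by cost and check for dominance;
- report the incremental ratios of intervention 1 against control and of intervention 2 against intervention 1, each with an interval;
- keep intervention 2 against control as a descriptive figure.

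The cost is one more contrast and a few lines of text, with no new data and no change in sample size. The added ratio may be imprecise, because its denominator is a difference between two active arms and could be near zero. It may also show intervention 2 less favourably than the ratio against control.
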